## 2 Detailed description of the study

### 2.1 Literature review:

Severe Acute Malnutrition (SAM) affects approximately 19 million children under the age of 5 and is associated with between one and two million preventable child deaths each year [1, 2]. In most developing countries, Case Fatality Rates (CFRs) in hospitals treating SAM remain at 20-30% many years after the standardised WHO protocol has become available and few of those requiring care actually access treatment [2-4]. SAM is defined as a weight-for-height measurement of 70% or less below the median, or three Standard Deviations (SD) or more below the new WHO growth standard, the presence of bilateral pitting oedema of nutritional origin, or a Mid-Upper-Arm Circumference (MUAC) of less than 11.5 cm in under five children [5]. In community based programme, the definition of SAM is based mainly on MUAC and presence of bilateral pitting oedema as described above[5].

Community-based management of SAM (CMAM) has been developed to offer a new approach to delivering care to acutely malnourished children in emergency situations and in more stable settings[6, 7]. The model is rooted in public health principles of coverage and access and is designed to achieve population-wide impact [8]. It focuses primarily on treatment of the majority of the acutely malnourished people as outpatients in their homes rather than in Therapeutic Feeding Centres (TFCs)[8]. Intensive inpatient care is also provided for those who have complications[8]. Techniques of community mobilisation are used to engage the affected population and achieve high proportion of early presentation while maximising coverage[8].

A recent United Nations (UN) joint publication summarizing experience with the community-based management of SAM concluded that CFRs of lower than 5% can be achieved through community-based management of SAM [5, 9]. CFR among 23,511 unselected severely malnourished children treated in 21 CTC programmes in Malawi, Ethiopia, and Sudan was 4.1%; with recovery rate and default rate of 79.4% and 11.0% respectively [9, 10]. Several recent studies have demonstrated the effectiveness of the CMAM in Malawi [11-16] and in other countries in Africa and Asia[17-22].

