#### Principal secondary hypotheses:

- 1 Weight gain (g/kg/day) during of children aged 6 to 59 months with SAM treated with FSMS-RUTF is not inferior to that of children with SAM of same age treated with MSMS-RUTF nor to that of those treated with P-RUTF with the fixed non-inferiority margin being 1.5g/kg/day (age group 6 to 23 months and 24 to 59 months to be sampled and analysed separately)
- 2 Time to recovery under treatment from admission to recovery of children aged 6 to 59 months with SAM treated with FSMS-RUTF is within the non-inferiority margin of 14 days when compared to children of the same age treated with MSMS-RUTF or to P-RUTF (age group 6 to 23 months and 24 to 59 months to be sampled and analysed separately).
- 3 Height gain during recovery and 3 months after discharge of children aged 6 to 59 months (admission age) with SAM treated with FSMS-RUTF is not inferior to that of children with SAM of the same age treated with MSMS-RUTF nor to that of children treated with P-RUTF given a fixed non-inferiority margin of 0.5 cm (age group 6 to 23 months and 24 to 59 months to be sampled and analysed separately)
- 4 Proportionally to body weight, percentage of body fat mass (BFM) measured at the time of recovery of children treated with FSMS-RUTF will not be higher than the percentage of BFM in children treated with MSMS-RUTF nor higher than the percentage of BFM of those treated with P-RUTF at the fixed margin of inferiority of 6%.
- 5 Tissues electrical properties assessed by Bio-electrical impedance analysis (BIA) will not be impaired in children treated with FSMS-RUTF when compared to that of children treated with MSMS-RUTF or with P-RUTF given a margin of equivalence to be determined by the synthesis methods based on findings of the SMS-RUTF study recently completed in DRC.

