#### 2.5.1.2 Efficacy trial

As stated in the hypotheses the main study will be a 3 group statistician blinded, randomized and controlled, parallel groups, **efficacy** non-inferiority trial. Because the participants will be able to distinguish the different RUTFs based on colour and mouth feel, participants will not be blinded. We will use the day care approach to ensure that children eat only the RUTF of the group to which they have been assigned. No study food will be taken home and the intake will be supervised by study enumerators who will in person feed the children.

The principal endpoints for the efficacy trial are:

1. Recovery rate
2. Mean weight gain
3. Mean time to recovery
4. Mean height gain
5. Percentage of body fat mass at recovery

6. Mean phase angle
7. Prevalence of anaemia
8. Incidence of deaths after discharge

The definition of principal endpoints is given below

(a) Recovery rate

The recovery rate will be measured as a percentage of those children who are discharged cured from the OTP programme divided by the total number of children who exit from the programme

$$\text{Recovery rate} = \frac{\text{No. children discharged Cured}}{\text{Total No. of Exit}} \times 100$$

(b) Average weight gain

The average weight gain will be measured as the mean of the growth velocity expressed in g/kg/day of individual children calculated as follow:

$$\text{Weight gain} = \frac{\text{Discharge weight (g)} - \text{Admission weight (g)}}{\text{Admission weight (kg)} \times \text{Length of stay (days)}}$$

$$\text{Average weight gain} = \frac{\Sigma \text{ weight gains}}{\text{Total children}}$$

(c) Average time to recovery or Length of stay

The average length of stay (LOS) is the mean of the LOS expressed in days of individual children calculated as follow:

$$\text{Average LOS} = \frac{\Sigma (\text{Discharge date} - \text{Admission date})}{\text{Total of children}}$$

(d) Average height gain

The average height gain is the mean of the height gain expressed in centimetres of individual children calculated as follow:

$$\text{Average height gain} = \frac{\Sigma (\text{Height 3 months after discharge (cm)} - \text{Admission height (cm)})}{\text{Total of children}}$$

(e) Prevalence of anaemia

The prevalence of anaemia will be expressed in percentage and calculated as follow

$$\% \text{ anaemia} = \frac{\text{n haemoglobin} < \frac{11.0\text{g}}{\text{dl}} * 100}{\text{total children with results}}$$

(f) Incidence of death after discharge

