**Table 2: Sample size according to the specific objective for the efficacy study**

| Specific objective | endpoint                                           | Research design                   | Assumptions                                                                                                      | Calculated sample                               |
|--------------------|----------------------------------------------------|-----------------------------------|------------------------------------------------------------------------------------------------------------------|-------------------------------------------------|
| SO1                | Recovery rate
6-23 months                       | Non-inferiority
clinical trial | Recovery rate
P-RUTF, FSMS-RUTF, MSMS-
RUTF= 75.5%
Non-inferiority margin=10%
Loss to follow up =10% | 250 per arm.
Total=750 SAM children          |
| SO2                | Recovery rate
24-59 months                      | Non-inferiority
clinical trial | Recovery rate P-RUTF, FSMS-RUTF,
MSMS-RUTF = 88.2%
Non-inferiority margin=10%
Loss to follow up =10%    | 150 per arm.
Total=450 SAM children          |
| SO3                | Mean
weight gain
6-23 months                 | Non-inferiority
clinical trial | Standard deviation=4.1
non-inferiority margin =1.5g/kg/d
Loss to follow up=10%                             | 110 children/arm
Total=330 SAM children      |
| SO4                | Mean
weight gain
24-59 months                | Non-inferiority
clinical trial | Standard deviation=3.5
non-inferiority margin =1.5g/kg/d
Loss to follow-up=5%                              | 75 children/arm
Total=225 children           |
| SO5                | Mean
Length of stay
6-23 months              | Non-inferiority
clinical trial | Standard deviation=22.8
non-inferiority margin = 14 days
Loss to follow up=10%                             | 40 children/arm
Total= 120 children          |
| SO6                | Mean
Length of stay
24-59 months             | Non-inferiority
clinical trial | Standard deviation=9.9
non-inferiority margin = 14 days
Loss to follow up=10%                              | 30 children/arm
Total= 90 children           |

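### Time to recovery is computed as mean length of stay over an unrestricted total of children, so it mixes speed of recovery with type of treatment failure and can be biased in either direction

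*Protocol*

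**What the plan says.** The hypothesis, in Section 1.2 and again in Section 2.3.2.2 (principal secondary hypothesis 2), concerns "Time to recovery under treatment from admission to recovery of children aged 6 to 59 months with SAM treated with FSMS-RUTF", to be shown non-inferior within 14 days of each comparator. Section 2.5.1.2 lists the endpoint as "Mean time to recovery". Item (c) of that section is headed "Average time to recovery or Length of stay" and reads "The average length of stay (LOS) is the mean of the LOS expressed in days of individual children"; its formula sums discharge date minus admission date and divides by the total of children. Table 2 sizes the endpoint as mean length of stay, with "non-inferiority margin = 14 days".

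Elsewhere in Section 2.5.1.2 the denominators are distinguished: item (a) sets cured children against all exits, and item (e) counts only children with results. Item (c) carries no such limit. Kaplan-Meier, log-rank and Cox methods are named in Section 2.5.6.2.1 only for survival after discharge. Both intention-to-treat and per-protocol analyses are planned, and the per-protocol result decides if they conflict.

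**The concern.** Length of stay and time to recovery agree only for children who leave cured. For the rest, the formula takes the date of exit as if it were the date of recovery. A default or death on day 15 contributes 15 days, less than a cure at 2 months; a non-responder contributes about 90.

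The protocol expects such exits. Section 2.1 cites programme data with 4.1% case fatality, "with recovery rate and default rate of 79.4% and 11.0% respectively". Section 2.8 foresees withdrawal of children whose appetite is suppressed, a reaction reported for some legume- and cereal-based foods. Section 2.5.4.3.1 accepts that day care may raise absenteeism. Under the discharge criteria in Table 3, which must hold for 14 successive days, a stay shorter than 14 days cannot be a cure, yet item (c) averages it in.

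At stake is a principal secondary non-inferiority test. If early exits are more common on a new food, the endpoint moves in that food's favour and can hide slower recovery.

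**Working it through.** **The plan's own figure.** Table 2 gives 40 per arm for ages 6-23 months (SD 22.8, margin 14, 10% loss). With the protocol's formula, n = f × 2σ²/d², and f = (1.645 + 0.842)² = 6.18: 2 × 6.18 × 22.8² / 14² = 32.8, so 33, and 33/0.9 gives 37. A t-based version gives 34, then 38. The stated 40 is close to both. For ages 24-59 months (SD 9.9) the same steps give 7, then 8, against a stated 30; that errs on the large side and does not affect this point.

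**Inputs for the endpoint check.**
- Recovery 75.5% (Table 2, ages 6-23 months).
- Cure at about 2 months, taken as day 60; non-responders at 3 months, taken as day 90 (Sections 1.5.2.2 and 2.12).
- Death or default 4.1% + 11.0% = 15.1% (Section 2.1).
- Non-response by subtraction: 100 − 75.5 − 15.1 = 9.4%.
- Day of early exit: not in the protocol. Assumed 15, range 10 to 30.

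**Formulas.** Item (c) over all children: p(cured) × t(cured) + p(early exit) × t(early exit) + p(non-response) × 90. Alternative with a 90-day horizon: p(cured) × t(cured) + p(not cured) × 90.

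| Arm | Item (c), days | Difference | 90-day horizon, days | Difference |
|---|---|---|---|---|
| Reference | 0.755×60 + 0.151×15 + 0.094×90 = 56.0 | – | 0.755×60 + 0.245×90 = 67.35 | – |
| A: 10 points of recovery lost to early exit | 0.655×60 + 0.251×15 + 0.094×90 = 51.5 | −4.5 | 0.655×60 + 0.345×90 = 70.35 | +3.0 |
| B: 10 points lost to non-response | 0.655×60 + 0.151×15 + 0.194×90 = 59.0 | +3.0 | 70.35 | +3.0 |
| C: no loss, cures 14 days later | 0.755×74 + 0.151×15 + 0.094×90 = 66.6 | +10.6 | 0.755×74 + 0.245×90 = 77.92 | +10.6 |
| D: A with cures 14 days later | 0.655×74 + 0.251×15 + 0.094×90 = 60.7 | +4.7 | 0.655×74 + 0.345×90 = 79.52 | +12.2 |

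**Range over the assumed exit day.** In A the difference is 0.10 × (exit day − 60): −5.0 at day 10, −3.0 at day 30. In D it is 0.655 × 14 = 9.17 plus that amount: +4.2 to +6.2. The starting split between early exit and non-response cancels out of these differences. With Table 2's 10% loss as the early-exit share, A still gives −4.6 at day 14 and −3.0 at day 30.

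**Cured children only.** In A and in B the mean is 60 days in both arms, a difference of 0 despite 10 points fewer recoveries. If the children who fail are the slower ones, the worse arm's mean falls below 60.

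**Against the margin.** Assume Table 2's SD of 22.8 applies and 250 × 0.9 = 225 children per arm. The standard error is 22.8 × √(2/225) = 2.15. In D the one-sided 95% upper limit is about 4.7 + 1.645 × 2.15 = 8.2 days, well inside 14.

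**The case against.** The strongest reply is that the protocol never says deaths and defaulters enter item (c). The hypothesis speaks of recovery, and item (d) uses the same loose denominator for height 3 months after discharge, which cannot include children who died or were lost. Table 2's SD of 9.9 days in older children also sits poorly with an all-exit mean: with 88.2% leaving at day 60, 10% at day 15 and 1.8% at day 90, the SD is already about 14. That check weakens if older children recover sooner, and the 22.8 for younger children does not discriminate. The cured-only reading is therefore possible. It does not rescue the rule, because it selects children on outcome.

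The second reply concerns direction, and it stands. Section 2.1 reports that the earlier milk-free food failed younger children through non-response, and non-responders stay 3 months. In that pattern item (c) moves against the new food. A reader might infer that the endpoint always favours the new food; the documents do not support that.

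Third, a reader might infer that the distortion alone would reverse a non-inferiority conclusion. It would not: −4.5 and +3.0 days are both well inside 14 days. An arm 10 points lower on recovery also sits at the margin of the primary endpoint, which is meant to detect it.

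Fourth, a per-protocol set might exclude defaulters, and a statistical analysis plan may say how. The protocol does not define that set, deaths might remain in it, and the intention-to-treat result is reported as well. The point rests on a formula the protocol itself states, not on detail left for later.

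**Conclusion.** The point holds as a conflict between the hypothesis and the formula that serves it. As written, item (c) does not measure time to recovery; the difference between arms combines speed of recovery with how children fail. The illustrated shift from a 10-point loss of recovery runs from 5.0 days too fast to 3.0 days too slow, depending on the type of failure. The more serious effect is masking: cures 14 days later, combined with 10 points more early exits, show as 4.2 to 6.2 days and would pass the margin easily.

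These sizes rest on single days for cure (60) and non-response (90), an assumed early-exit day, and an assumed 10-point difference. They show what the rule can do and do not predict this trial's result. Because the endpoint is a principal secondary one, the definition should be corrected, but the primary conclusion does not depend on it.

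**What to change.** Replace item (c) with an endpoint that has recovery as the event over a fixed 90-day horizon, in all randomised children, with death, default and withdrawal counted as not recovered. One suitable form is the restricted mean time to recovery to day 90, taken from the cumulative incidence of recovery. Align the wording of the hypothesis, the endpoint list and Table 2 with it.

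State that the 14-day margin applies to this measure, and justify or re-derive it. Section 2.3.3 supports 14 days only by its use in an earlier study. Setting failures to 90 days makes the measure overlap with the recovery rate: with every cure at day 60, each failure costs 30 days, so a 14-day difference would need a recovery deficit of 14/30, about 47 points. At equal recovery of 75.5%, it would need cures delayed by 14/0.755 = 18.5 days.

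Report observed length of stay descriptively, overall and among cured children.

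The cost is a little extra analysis and a restated rationale for the margin. Dates and type of discharge are already collected (Table 4), and the planned 250 and 150 per arm far exceed the 40 and 30 that Table 2 asks for on this endpoint.

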## 2.5.2 Study populations

### 2.5.2.1 Acceptability trial

Children aged 3 to 5 years regularly attending the selected CBCC with signs of moderate acute malnutrition as defined by MUAC between 11.5 and 12.5 cm will be eligible for the acceptability trial. The other eligibility criteria include absence of bilateral pitting oedema, absence of any disability, absence of any acute illness, absence of skin lesions, absence of mouth lesions, permanent resident of the area residing at a maximum radius of 30 minutes walk with no plan to travel during the period of the study, and parent or caregiver consent. Two CBCC will be used for the study. Each site will be testing a separate study food.

### 2.5.2.2 Efficacy trial

The eligibility criteria for inclusion into the study are:

- Age between 6 months and 59 months
- Presence of SAM defined by MUAC<115mm or presence of bilateral pitting oedema of any grade or presence of clinical signs of wasting confirmed by the supervisor.
- Residing within 1 hour walking distance from the day-care centre
- Caregivers consent to participate

The exclusion criteria for children meeting these criteria include:

- Presence of disability including congenital or acquired disorders affecting growth
- Refusal to participate (children who refuse to participate will be referred to the existing outpatient therapeutic feeding sites not participating into the study)
- Children of visiting families who risk to return to their location before completing the study that include the therapeutic feeding phase and follow up after discharge phase. These children will also be referred to the non participating outpatient therapeutic feeding sites.
- Children with history of any food allergy
- Child with previous admission for severe acute malnutrition in the previous 3 months (will be referred to non participating outpatient therapeutic centres)

Children who present with SAM with complications will be first referred for inpatient care and enrolled into the study after stabilisation if they meet eligibility criteria. Children not assessed by study team prior to admission into the stabilisation centre will not be eligible. Children with HIV or tuberculosis meeting criteria for outpatient management will be linked to the nearest health facility providing comprehensive treatment of these diseases and included into the research despite the presence of these chronic infections. The research team will ensure adherence to both the medical treatment and the nutrition treatment.

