### **1.5.2.2 Efficacy trial**

Children staying within 1 hour walking distance from feeding points especially established in the community for the study will be enrolled and will be followed up from admission to nutrition recovery using a day care approach. Enrolled children will attend the site daily from 9 am to 3 pm. Children will be offered 200kcal/kg/day of one of the study RUTF. Children will be declared non-recovered if they don't meet the discharge criteria ( $MUAC \geq 12.5$  cm and no oedema) after 3 consecutive months of treatment. Apart from the difference in study therapeutic food, children of all the three study groups will be treated in the same way in accordance with the national guidelines for the treatment of SAM but using the day-care approach as stated above. The day-care approach allows the elimination of several confounding factors such as sharing or poor intake of the therapeutic food at households' level, inappropriate intake of routine medicines and differences in the product acceptance by caregivers that may affect child feeding of the study food. This approach will also allow close monitoring of side effects such as abdominal pain due to iron intake, flatulence (due to unabsorbed sugar), diarrhoea due to lactose intolerance and appetite suppression due to some oligosaccharides. Anthropometric parameters will be measured daily (weight and MUAC) or weekly (height). Clinical conditions will be assessed daily (appetite, oedema, cough, difficulty of breathing, diarrhoea, dehydration, fever, skin eruption, neurological status, anaemia). Embedded sub-studies will allow the assessment of

- haemoglobin (admission and discharge) with an Haemocue device that uses capillary blood collected at finger prick;
- body composition using deuterium dilution technique (at discharge for both those who recovered and those who did not recover);
- body composition using bio-electrical impedance analysis (at admission or when oedema subside, at time of reaching discharge criteria, at discharge and at 3 months follow up) using a Bodystat 1500 MDD device;
- breast milk intake using the dose-to-mother deuterium oxide dilution technique in children still breastfed at admission (two weeks after the start of the treatment);
- stool calprotectin using a quantitative point-of-care chromatographic immunoassay kit for the assessment of intestinal inflammation (admission, 28 days after the start of treatment, at discharge)

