## 2.4 Setting

The research programme will be conducted in the Central Region of Malawi. For the acceptability trial, two CBCCs will be used for the study. We have pre-agreement with several CBCCs but the final choice of the CBCCs will be made in January 2015 based on the functionality and on the number of children attending the centres at that time. The efficacy trial will be carried out in 3 Health District of the Central Region as recommended by the Ministry of Health. These Health Districts are Lilongwe, Dedza and Mchinji. Pre-agreement have been secure with the District Health Officers (DHO) of these Health Districts. In each Health District, a Cluster (a sub-administrative area in Malawi administrative organisation) with the highest burden of acute malnutrition according to the 2014 monthly routine statistics will be selected. In total, 30 community based feeding centres will be established (10 in each District) in the catchment areas of OTP sites that reported more than 60 admissions of SAM cases in 2013. The list will be finalised based on the 2014 statistics and after a field visit has cross-checked the routine statistic figures. The Central region has the worst indicators for undernutrition among under-five children. During the 2010 Malawi Demographic Survey, the prevalence of stunting was 47.2% while that of underweight was 13.5%. The prevalence of wasting is low at 1.8% for severe wasting and 4.3% for wasting. However, this figure underestimates the actual incidence of SAM because up to 80% of cases are oedematous in Malawi and they are not included in these statistics[93]. Indeed, according to

Ministry of Health, by the end of August 25,313 children with SAM had been admitted to CMAM in 2013/2014 consumption year (UNICEF, Malawi situation report, July and August 2014).

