**Table 3. Admission and discharge criteria for 6 to 59 months old children**

|                  |                                                                   |
|------------------|-------------------------------------------------------------------|
| Admission | MUAC < 115mm                                            |
|                  | Bilateral pitting oedema grade + or ++                     |
|                  | WFH Z-score < - 3 (WHO 2006 curves)                     |
| Discharge | Absence of bilateral pitting oedema for 14 successive days |
|                  | MUAC <math>\geq 125</math>mm for 14 successive days        |
|                  | Absence of acute life threatening infection                |

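### Children who enter by wasting signs or weight-for-height may already be at MUAC 125 mm without oedema, so they count as recovered without responding to the food and narrow the primary comparison

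*Protocol*

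**What the plan says.** **Entry.** Protocol section 2.5.2.2 lists three alternative routes: "Presence of SAM defined by MUAC<115mm or presence of bilateral pitting oedema of any grade or presence of clinical signs of wasting", the last to be confirmed by the supervisor. Table 3 (section 2.5.4.3.2) gives MUAC below 115 mm, oedema of grade + or ++, and "WFH Z-score < - 3 (WHO 2006 curves"). Neither list, nor the exclusion criteria, sets an upper MUAC limit for a child who enters by a route other than MUAC.

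**Recovery.** Section 1.5.2.2 states: "Children will be declared non-recovered if they don't meet the discharge criteria", gives those criteria as MUAC of at least 12.5 cm and no oedema, and applies them "after 3 consecutive months of treatment". Table 3 requires "Absence of bilateral pitting oedema for 14 successive days", MUAC of at least 125 "mm for 14 successive days", and no acute life-threatening infection. Neither version asks for weight gain, a weight-for-height threshold or any change from admission.

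**Endpoint.** Section 2.5.1.2: "The recovery rate will be measured as a percentage of those children who are discharged cured from the OTP programme", divided by all exits. The primary hypotheses (section 2.3.2.2) require this rate to exceed 75% with FSMS-RUTF and to be non-inferior within 10 points, in each age group.

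**Related analyses.** Section 1.5.4.2 plans a subgroup by oedematous or non-oedematous malnutrition. The protocol restricts or separates nothing by admission MUAC.

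**The concern.** Entry and recovery use different yardsticks. A child can be admitted because of wasting signs or low weight-for-height and then be judged on MUAC and oedema, which may have been satisfactory from the start. Such a child is counted as recovered in whichever arm it falls and says almost nothing about the food.

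In a superiority trial this would cost power. In a non-inferiority trial it moves the result towards the claim: the observed difference shrinks while the margin stays at 10 points. The same children raise the rate compared with 75%. They also contribute near-identical short times to the time-to-recovery comparison. Relying on the per-protocol analysis when the two analyses disagree (section 2.5.6.2.1) does not help, because these children can be fully compliant.

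An oedematous child with MUAC of at least 125 mm is a partial case. The MUAC part is already met, but the oedema must still clear.

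**Working it through.** **1. Inputs.** From Table 2: 250 per arm at 6-23 months, assumed recovery 75.5% in all arms, margin 10 points, loss to follow-up 10%. From sections 1.5.3.2 and 2.5.3.1: power 80%, one-sided 95% confidence limit. Evaluable per arm: 250 x 0.9 = 225.

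**2. The plan's own figure.** n = (1.645 + 0.842)^2 x 2 x 0.755 x 0.245 / 0.10^2 = 229. With 10% loss, 229/0.9 = 255, or 229 x 1.1 = 252. The stated 250 is reproduced closely, so one-sided 5% is the right setting for what follows.

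**3. Dilution model.** Let q be the share who recover in every arm whatever the food, and D the deficit among the others. The overall deficit is (1 - q)D. The chance of declaring non-inferiority is Phi[(0.10 - (1 - q)D)/SE - 1.645], with unpooled SE. The protocol gives no q, so its values are assumptions. D = 0.10 throughout.

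*Control rate held at 75.5% overall:*
- q = 0: 5.0%.
- q = 10%: experimental rate 0.755 - 0.09 = 0.665; SE = sqrt[(0.755 x 0.245 + 0.665 x 0.335)/225] = 0.0426; Phi(0.01/0.0426 - 1.645) = 7.9%.
- q = 20%: experimental rate 0.675; SE = 0.0424; Phi(0.02/0.0424 - 1.645) = 12.0%.

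*Assured recoveries also raise the overall rate:*
- q = 10%: rates 0.10 + 0.90 x 0.755 = 0.7795 and 0.10 + 0.90 x 0.655 = 0.6895; result 8.0%.
- q = 20%: rates 0.804 and 0.724; result 12.7%.

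At 24-59 months (88.2%, 150 x 0.9 = 135 per arm) the two versions give 7.8-7.9% at q = 10% and 11.7-12.3% at q = 20%.

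**4. What the margin then tolerates.** An overall deficit of 10 points corresponds to 10/(1 - q) points in the other children: 11.1 at q = 10% and 12.5 at q = 20%.

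**5. The 75% threshold.** An overall rate of 75% needs only (0.75 - q)/(1 - q) among the other children: 0.65/0.90 = 72.2% at q = 10%, and 0.55/0.80 = 68.8% at q = 20%.

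**6. Cost of restricting the comparison.** With 225(1 - q) evaluable per arm and 75.5% recovery in both arms, power is Phi[0.10/sqrt(2 x 0.755 x 0.245/(225(1 - q))) - 1.645]: about 79% at q = 0, 76% at q = 10% and 71% at q = 20%. Restoring 80% would need about 255/(1 - q) enrolled per arm, that is 284 or 319.

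**The case against.** **The stated hypothesis concerns all children with SAM.** If 20% recover regardless and the rest have a 10-point deficit, the deficit in the whole population is 8 points. That lies inside the margin, so declaring non-inferiority is correct for the hypothesis in section 2.3.2.2. This stands. A reader might infer that the type I error of the stated hypothesis is inflated, and the documents do not support that. The percentages above are errors only with respect to children who need MUAC gain. For that group the trial is less able to detect a deficit.

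**Oedematous children are not assured recoveries.** Since the protocol says that "up to 80% of cases are oedematous in Malawi", a reader might infer that most of the sample is uninformative. It does not follow. The figure says nothing about how many of them have MUAC of at least 125 mm. These children must still clear oedema, which may depend on the food, and default and death count against recovery. For them the dilution figures are upper bounds. If form of SAM shows a significant interaction, section 1.5.4.2 also allows the analysis to be adjusted, although that would not isolate entrants by wasting signs or weight-for-height.

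**The group that fully meets the rule at entry may be small.** Section 2.1 says that community programmes define SAM mainly by MUAC and oedema, and the weight-for-height route is in Table 3 but not in the eligibility list. This stands, and no value of q can be defended from the protocol. Recovery on day 0 likewise rests on the shorter rule in section 1.5.2.2, whereas Table 3 requires the 14-day hold.

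**Analysis sets are often left to the SAP.** True, and their absence is not the point here. The point is the pairing of entry and recovery rules, which the protocol itself fixes.

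**Conclusion.** The mismatch is real under either recovery rule, and its direction is clear. Non-oedematous children admitted at MUAC of at least 125 mm add near-automatic recoveries to every arm, pull the difference towards zero and lift the rate tested against 75%. No analysis in the protocol isolates them.

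The size is unknown because q is not given. Under the assumption of a true 10-point deficit in the other children, the chance of declaring non-inferiority at 6-23 months rises from 5% to about 8% at q = 10% and 12-13% at q = 20%. This assumes that the affected children recover in all arms. It does not show that the primary hypothesis as written would be wrongly accepted, nor that the bias is large. It is an inexpensive improvement to what the primary comparison can show.

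**What to change.** 1. Leave children who at admission already have MUAC of at least 125 mm and no oedema out of the recovery-rate and time-to-recovery comparisons, and report them separately by arm. The restriction uses baseline data only, so the randomised comparison is preserved. State that the comparison then applies to children not already at the recovery threshold.
2. Prespecify a sensitivity analysis of the primary comparison in children with admission MUAC below 125 mm. Report its confidence interval against the 10-point margin, and limit any claim about growth recovery to what it supports. Do not add a veto on the point estimate: at a true deficit of exactly 10 points it would trigger only about half the time.
3. Reconcile the entry lists in section 2.5.2.2 and Table 3 (weight-for-height, wasting signs, oedema grade), and the recovery rules in section 1.5.2.2 and Table 3 (14-day hold, infection).

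**Cost.** Items 1 and 2 need protocol or SAP wording only, because Table 4 already records MUAC and oedema at admission. The downside is a loss of precision that grows with q, as calculated above, and it should be stated. These two items change no treatment, admission or discharge rule.
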